## Methods and analysis

### Study design

Contemporary evaluations of the effectiveness of health policies go beyond estimating their total effect on outcomes. Mediation analysis decomposes the total effect of an intervention into separate causal pathways,^31^ enabling an understanding of why and how policies work by estimating the direct and indirect effects of the exposure.^32^ We will conduct mediation analyses investigating the potential mediators of the impact of QP on antibiotic prescribing in primary care in England, establishing the direct and indirect effects of the QP initiative.

### Data sources

The study will constitute secondary analyses of antibiotic prescribing data from NHS England covering the period 2013 to 2018. CCGs were established in England in April 2013 following the Health and Social Care Act 2012.^33^ Data on antibiotic prescribing in primary care at CCG level will be sourced from the NHS England Antibiotic Quality Premium Monitoring Dashboard, which is produced by the NHS Business Services Authority (BSA).^34^ Primary Care prescribing data are publicly available from the NHS BSA website. The dataset contains the number of antibiotic items (STAR-PU) prescribed in each CCG from the financial year 2015/2016 to 2018/2019, with data for October 2018 the latest at the time of this protocol. Data for the period 2013 to 2015 will be mapped to CCG level from the practice-level data.

Practice-level antibiotic prescribing data will be sourced from OpenPrescribing, an Evidence-Based Medicine DataLab project by the University of Oxford. OpenPrescribing publishes monthly antibiotics prescribing data from August 2013, with data for October 2018 the latest at the time of this protocol. Practice-level antibiotic prescribing data from OpenPrescribing is not STAR-PU weighted, so the extracted data will be STAR-PU weighted using figures from the 2013 Item-based age–sex weighting for oral antibacterials^14^ and the number of registered patients in each age–gender category in a practice for each specific month.

Overall, the dataset offers coverage of at least 3 years postintervention given that antibiotic prescribing became a QP priority in March 2015. This will be important in investigating the immediate direct and indirect effects of the QP initiative while giving an insight into the sustainability of the identified effects (if any) in the long-term.

### Variables

The predictor will be a binary variable indicating the implementation of the QP intervention. The intervention will include all periods after March 2015 when the 2015/2016 QP guidance in England was published, while the control will be periods prior to this. The primary outcome of interest is the rates of antibiotic prescribing at CCG level in England, which will be a continuous variable indicating the number of items (per STAR-PU) prescribed per month.

To account for differences in practice and CCG characteristics that can contribute to variance in antibiotic prescribing, we will be adjusting for the number of general practitioners in each practice (from the NHS Workforce data),^35^ the index of multiple deprivation (from the Department for Communities and Local Government),^36^ prevalence of comorbidities (asthma, chronic obstructive pulmonary disease, diabetes, cancer, chronic kidney disease (from the NHS Quality and Outcomes Framework database)),^37^ the prescribing rate of other non-antibiotic drugs (opioids and benzodiazepines) and seasonal influenza vaccination rate (from PHE).^38^

Mediator variables will be derived from the questionnaire data from a PHE survey,^39^ with 187 of the 209 AMS leads representing CCGs in England and data from other organisations that have evaluated the interventions treated as potential mediators in this study. In the PHE survey, participants were required to complete questionnaire items, which included their adoption of national and local strategies in their respective CCG to enable them to meet QP targets on antibiotic prescribing in primary care. The mediator variables will be binary or continuous variables, indicating the adoption of key interventions and intermediaries that are hypothesised to reflect in the integration of the QP guidance in improving antibiotic prescribing in primary care practices.

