Interventions such as antibiotic stewardship programmes, education and training initiatives targeted at prescribers and patients, financial incentives, among others have been implemented in England to reduce AMR through reduced prescribing. In particular, the Quality Premium (QP) is a National Health Service (NHS) England initiative established in 2013 to reward Clinical Commissioning Groups (CCGs) financially based on the quality of specific health services considered to be of national or local priority and commissioned over a specific period.^17^ Improvement of antibiotic prescribing in primary care was one of the national priorities in the 2015/2016 guidance,^18^ constituting 10% of the premium awarded from 2016/2017 to date.^19 20^ Key aspects of the ‘improved antibiotic prescribing’ priority are reductions in the number of antibiotics prescribed in primary care facilities across England and in the proportion of broad-spectrum antibiotics prescribed in primary care (2015–2017).^19^ Part of the requirements in the 2015/2016 QP guidance for demonstrating improved antibiotic prescribing by CCGs was a reduction in the number of antibiotics prescribed in primary care by 1% of the mean value in England in 2013/2014 (ie, 1.61 items per Specific Therapeutic group Age-sex Related Prescribing Unit (STAR-PU)). This was further increased to 4% in the 2016/2017 guidance.

Emerging evidence suggests a reduction in antibiotic prescribing in primary care practices in the UK following the QP initiative.^21 22^ Prescribing data from England show a reduction of about 2.7 million antibiotic items between 2014/2015 and 2016/2017 financial year.^23^ Eighty-eight per cent of the CCGs in England achieved the target of reducing antibiotic prescribing in the first 2 years of QP.^21^ Also, there has been a significant reduction in the proportion of broad-spectrum antibiotics prescription with 83% of the CCGs meeting their target in the first 2 years.^21^ Such reductions in antibiotic prescribing would be expected to contribute to reductions in the development of resistance.^24^ However, little is known about the mechanisms by which the QP initiative impacted on antibiotic prescribing in primary care practices.

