### Statistical analysis

Our first analysis will be an interrupted time series to investigate whether antibiotic prescribing rate in England has changed over time, and how such changes, if any, are associated with the QP implementation in March 2015. This will be conducted using the ordinary least square regression method^41^ to assess whether the 2015/2016 QP establishment resulted in a shift in the level and trend in antibiotic prescribing in primary care in England compared with the period before the intervention. Using the practice-level dataset, a univariate time series with the mean antibiotic items (STAR-PU weighted) prescribed in all primary care practices in England for each month will be conducted using the *ITSA* function on Stata, with post-trend specification to show a postintervention trend. The Cumby-Huizinga general test for autocorrelation will be used for general specification test of serial correlation in the time series data.^42^

A new QP guideline was implemented each financial year with changes in the prescribing rate target and the proportion that improved prescribing constituted in the QP award for each year. Our mediation analyses will investigate the effects of the QP by comparing antibiotic prescribing rate in the financial year before its implementation to each subsequent year postimplementation; as such, our dataset for the mediation analyses will have the control group as the financial year before QP and the intervention group as a specific post-QP implementation year. Three analyses will be conducted for each of the three financial years since QP establishment. This will enable us to compare the effects of the different target levels that have been set over the years and the proportions of the QP award attributed to improvement in antibiotic prescribing.

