### Sensitivity analyses

Sensitivity analyses using dummy implementation dates of 1 to 3 months before and after the actual month each of the QP guidance were published will be conducted to assess the difference between the time the guidance is published and the dissemination of information and development of local arrangements by the CCGs. These analyses will further help to investigate the anticipatory effect of the policy and whether lag in implementation attenuates the effect of the intervention.

Also, we will conduct separate analysis with the outcome variable (antibiotic prescribing rate) as a binary variable (indicating whether each CCG achieved the required rate of reduction in antibiotic prescribing as stated in the QP guidance for each year) to examine whether the classification of the outcome variable based on achievement of QP target influences the results.

Subgroup analyses will be conducted on clusters of primary care practices based on their antibiotic prescribing behaviour (high and low prescribers) and indices of deprivation to examine whether any effect of the QP initiative seen in the overall population is different in subgroups of practices. The top and bottom 20% antibiotic prescribers as of March 2015 will be categorised as high and low prescribers. To address the issue of regression to mean in subgroup analyses, we will build a separate model with categorisation into high and low prescribers based on the mean of the prescribing rate of practices in the last 3 months to March 2015. The use of mean of multiple measures will offer a better estimate of each practice’s true mean before the 2015/2016 QP initiative.^48^ The subgroup analysis based on the indices of deprivation data^36 49^ at primary-care practice level will be important in establishing the equity impact of the QP initiative.

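### The interrupted time series has no term for days or working days in the month, which costs precision and lets the dummy-date estimates move when there is no true effect

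*Protocol article*

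**What the plan says.** The Variables section sets the primary outcome at CCG level, "which will be a continuous variable indicating the number of items (per STAR-PU) prescribed per month". In Data sources, the practice-level counts are STAR-PU weighted using the "number of registered patients in each age–gender category in a practice for each specific month". That standardises for list size and age-sex mix, not for the length of the month or the number of days on which services are open.

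Under Statistical analysis, the first analysis is a univariate series of the "mean antibiotic items (STAR-PU weighted) prescribed in all primary care practices in England for each month". It is fitted by ordinary least squares with a level and a trend change and a test for serial correlation. No seasonal, day-count or working-day term is named, and the covariates listed under Variables include no calendar variable.

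The timing is fixed in two places: "OpenPrescribing publishes monthly antibiotics prescribing data from August 2013, with data for October 2018 the latest" (Data sources) and "The intervention will include all periods after March 2015 when the 2015/2016 QP guidance in England was published" (Variables).

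The Sensitivity analyses section then uses "dummy implementation dates of 1 to 3 months before and after the actual month each of the QP guidance were published" to look for anticipation and implementation lag.

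For scale, the Introduction gives the 2015/2016 requirement as "a reduction in the number of antibiotics prescribed in primary care by 1% of the mean value in England in 2013/2014", with 4% in the following year's guidance.

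**The concern.** Months run from 28 to 31 days. With moving weekends, Easter and bank holidays, working days per month run from 18 to 23 over the study window. One day is about 3.3% of an average month and one working day about 4.7%. If prescribing or dispensing follows either count, the monthly outcome carries variation of several per cent that has nothing to do with the QP, while the policy targets are 1% and 4%.

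Two things are at stake. First, this variation goes into the residual and widens the interval for the level change. Second, moving the start date by a month moves a short or long month from one side of the break to the other. The estimate then changes with no true effect, in an analysis meant to show anticipation or lag.

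**Working it through.** The protocol states no precision or power figure for the time series, so there is nothing to reproduce. The check fits the planned model to a series that contains only the calendar.

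**Inputs**
- Window: August 2013 to October 2018, 63 months (Data sources).
- Break: after March 2015 (Variables). With April 2015 as first post month there are 20 months before and 43 after; with March 2015, 19 and 44. Both were run.
- Dummy dates: 1 to 3 months either side, so December 2014 to July 2015 covers both readings (Sensitivity analyses).
- Targets: 1% and 4% (Introduction).
- Assumption from outside the document: working days are Monday to Friday less England bank holidays. These are calendar facts.
- Assumption: items are proportional either to calendar days (lower case) or strictly to working days (upper case).

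**Size of the calendar variation**
- Calendar days: mean 30.44, SD 2.7% of the mean; one day = 1/30.44 = 3.3%.
- Working days: mean 21.10, SD 5.2% of the mean; one working day = 1/21.10 = 4.7%.

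**Model.** The series is y(t) = 100 × d(t) / mean(d), where d is the day count. The fit is y(t) = b0 + b1·t + b2·X(t) + b3·(t − t0)·X(t), with X = 1 from the first post month t0. The true b2 is zero.

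False level change b2 in percentage points (SE in brackets):

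| First post month | Calendar days | Working days |
|---|---|---|
| Dec 2014 | -0.02 (1.65) | -1.18 (3.15) |
| Jan 2015 | -0.63 (1.61) | -0.99 (3.08) |
| Feb 2015 | -1.16 (1.57) | -0.83 (3.02) |
| Mar 2015 | +1.34 (1.54) | +0.73 (2.97) |
| Apr 2015 | +0.69 (1.52) | -0.65 (2.92) |
| May 2015 | +1.05 (1.50) | +0.81 (2.88) |
| Jun 2015 | +0.47 (1.48) | +3.47 (2.80) |
| Jul 2015 | +0.84 (1.46) | +2.06 (2.79) |

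- At the planned date (March or April), b2 lies between -0.65 and +1.34, each value within one SE.
- The 95% half-width from the calendar alone, April start, is 1.96 × 1.52 = 3.0 points (calendar days) or 1.96 × 2.92 = 5.7 points (working days).
- The spread across the dummy dates is 1.34 + 1.16 = 2.5 points (calendar days) or 3.47 + 1.18 = 4.65, about 4.7 points (working days).

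**Adding 11 calendar-month indicators** (starts January to July 2015)
- Calendar days: residual SD falls from 2.75% to about 0.41%; b2 lies between +0.09 and +0.30.
- Working days: residual SD falls only from 5.28% to about 4.1%. The SE at April falls from 2.92 to 2.35. b2 lies between -0.50 and +1.22.

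Month terms remove nearly all of the month-length part. They leave most of the working-day part, because it moves from year to year.

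**Financial years**
- Calendar days: 365 in 2014/15, then 366, 365 and 365. Shifts: 1/365 = +0.27%, 0 and 0.
- Working days: 253 in 2014/15, then 252, 255 and 251. Shifts: -1/253 = -0.40%, +2/253 = +0.79% and -2/253 = -0.79%.

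**The case against.** The case against is substantial, and much of it stands.

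- **Yearly contrasts.** A reader might infer that calendar noise above the target also enters the financial-year comparisons that carry the mediation analysis. It does not. Whole years largely cancel the variation, and every shift is below 1%. In 2016/17, where the working-day shift is +0.79%, the target is 4%.
- **Bias.** A reader might infer a biased QP effect. At the planned date the false level change is within one SE on either scale.
- **Dummy dates.** The +3.5% comes from June 2015 alone, and its SE is 2.80. From December to May the working-day values stay between -1.2 and +0.8. Anyone reading these estimates with their standard errors would not call the movement anticipation or lag. The scatter remains, but a false conclusion is not inevitable.
- **Strict proportionality.** The Ethics and dissemination section says that the counts are dispensed items. It does not say that they follow working days, and catch-up around holidays would bring the noise nearer the lower case. The 2.9-point figure is therefore an upper case.
- **Month terms.** They would remove most of the date-to-date movement, and a fuller plan may contain them. The article names none and describes a univariate model, and month terms alone leave the working-day residual SD at about 4.1%.
- **Unit.** Items per STAR-PU is the unit of the policy target, so keeping it is sensible. This argues for a covariate rather than a rescaled outcome.

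**Conclusion.** The point holds for the interrupted time series and its dummy-date checks, as a matter of precision. As written, the model leaves calendar variation in the residual. That alone gives the level change a standard error of about 1.5 points (calendar days) to 2.9 points (strict working days). Both exceed the 1% target and both are below 4%. The dummy-date estimates can spread by about 2.5 to 4.7 points with no true effect.

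The documents do not support a claim of material bias at the planned date, or of a meaningful distortion of the financial-year contrasts.

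The range rests on two unverified proportionality assumptions, on the standard bank-holiday calendar, and on a series with no other noise. How much precision is lost in practice depends on the other residual variation, which the article does not give. This is a cheap improvement, not the correction of an invalid analysis.

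**What to change.** Keep items per STAR-PU per month as the outcome. In Statistical analysis, add the number of working days in the month as a covariate to the interrupted time series, together with calendar-month terms, and use the same model for every dummy date in Sensitivity analyses. A covariate estimates whatever working-day dependence exists, so strict proportionality need not be assumed. State also that differences between dummy dates will be read against their standard errors, since these estimates come from the same series.

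The cost is one added sentence and a public calendar; no new prescribing data are needed. The downside is 12 extra terms (one for working days, 11 for months) in a 63-point series. Residual degrees of freedom fall from 63 − 4 = 59 to 63 − 16 = 47.

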**Methods and analysis:**

The study will constitute secondary analyses of antibiotic prescribing data for almost all primary care practices in England from the NHS England Antibiotic Quality Premium Monitoring Dashboard and OpenPrescribing covering the period 2013 to 2018. The primary outcome is the number of antibiotic items per Specific Therapeutic group Age-sex Related Prescribing Unit (STAR-PU) prescribed monthly in each practice or CCG. We will first conduct an interrupted time series using ordinary least square regression method to examine whether antibiotic prescribing rate in England has changed over time, and how such changes, if any, are associated with QP implementation. Single and sequential multiple-mediator models using a unified approach for the natural direct and indirect effects will be conducted to investigate the relationship between QP initiative, the potential mediators and antibiotic prescribing rate with adjustment for practice and CCG characteristics.

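### The mediation models do not fix whether a row is a CCG-month or a CCG-year, or allow for repeated values from one CCG; with the monthly outcome and independent rows, null mediators could be declared well above 5% of the time.

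*Protocol article*

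**What the plan says.** The Variables section sets the primary outcome at CCG level, "which will be a continuous variable indicating the number of items (per STAR-PU) prescribed per month". The Abstract describes it as "prescribed monthly in each practice or CCG", which covers both the practice-level and the CCG-level work.

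The Statistical analysis section runs the interrupted time series on the practice-level dataset, as a national monthly mean. For the mediation work it plans on "comparing antibiotic prescribing rate in the financial year before its implementation to each subsequent year postimplementation", with "the control group as the financial year before QP and the intervention group as a specific post-QP implementation year". Each such dataset therefore holds the same CCGs twice. Single-mediator models are fitted with the Stata command medeff, adjusted for practice and CCG characteristics. Variables that show mediation go forward to a sequential multiple-mediator model. No row unit and no term for repeated CCG values is given.

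Mediators come largely from a survey of "187 of the 209 AMS leads representing CCGs in England". Under Sensitivity analyses the outcome is also coded as binary, "indicating whether each CCG achieved the required rate of reduction in antibiotic prescribing as stated in the QP guidance for each year".

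**The concern.** The time series uses a national mean from practice data, so the CCG-level monthly outcome can only serve the mediation models, which the Limitations section places mainly at CCG level. Read literally, each CCG then supplies up to 24 rows per model: 12 months in each of two years. A survey mediator holds one value per CCG, so 12 monthly rows add little information about its association with prescribing. Standard errors that treat those rows as independent would be too small.

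Single-mediator results decide which variables enter the joint model. An inflated screen would carry strategies with no effect into the reported mechanism of QP. The binary sensitivity analysis is affected too. Meeting a target happens once per CCG per year, so if the main model uses monthly rows, that analysis changes the row count as well as the coding. It could not then isolate the effect of classifying the outcome, which is its stated purpose.

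**Working it through.** The article gives no alpha, power, variance or intraclass correlation (ICC), so there is no figure to reproduce. A two-sided 5% test is assumed.

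**Inputs from the documents.** 209 CCGs, 187 with survey data (187/209 = 89.5%); two financial years per contrast; 12 months per year.

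**Row counts per contrast.**
- Yearly rows: 209 × 2 = 418; 187 × 2 = 374.
- Monthly rows: 209 × 2 × 12 = 5,016; 187 × 2 × 12 = 4,488. The ratio is 12.

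**Monthly rows treated as independent, mediator absent before QP.** The mediator coefficient then rests on the post-QP year, where each CCG supplies 12 correlated rows. Design effect D = 1 + (12 − 1) × ICC; actual error rate = 2 × [1 − Φ(1.96/√D)].

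| ICC (assumed) | D | Formula | Simulated, independent rows | Simulated, CCG-clustered |
|---|---|---|---|---|
| 0.02 | 1.22 | 7.6% | – | – |
| 0.05 | 1.55 | 11.5% | 10.4% | 4.9% |
| 0.3 | 4.3 | 34.5% | 36.2% | 5.6% |
| 0.5 | 6.5 | 44.2% | 45.0% | 4.1% |
| 0.7 | 8.7 | 50.6% | 50.8% | 6.2% |
| 0.9 | 10.9 | 55.3% | 53.8% | 6.2% |

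The simulation used 187 CCGs, 60% adoption after QP, no true mediator effect, 1,000 runs per ICC, and a regression of the outcome on QP and mediator. Yearly rows without clustering gave 3.8-5.9% here, because each CCG informs the mediator coefficient only once.

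**Some adoption before QP.** With about half the adopters already using the strategy, the same ICCs (0.05 to 0.9) gave 13.5-62.7% for independent monthly rows, 6.4-12.9% for independent yearly rows and 4.7-6.5% for CCG-clustered monthly rows.

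**Mediator identical in both years.** All 24 monthly rows then share one mediator value: D = 1 + 23 × ICC, which at ICC 0.9 is 21.7 and gives 67%. For yearly rows D = 1 + ρ, where ρ is the correlation between a CCG's two annual values: ρ = 0.7 gives 13%, and ρ near 1 gives 17%. A second simulation (between-CCG SD 6-14, CCG-year SD 2, monthly noise SD 3, seasonal amplitude 0 or 10, all as % of the mean rate) gave 51-68% for monthly and 13-18% for yearly rows. Its ICCs run from (36 + 4)/(36 + 4 + 9 + 50) = 0.40, taking the variance of a seasonal wave of amplitude 10 as 10²/2 = 50, to (196 + 4)/(196 + 4 + 9) = 0.96.

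All these rates concern the mediator-outcome path. They carry over to the indirect effect when QP clearly raises adoption. If the mediator is identical in both years, the QP-to-mediator path is zero, so the upper yearly figures describe that one path and not the whole indirect effect.

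**The case against.** A reader might infer that the article gives three conflicting definitions of its primary outcome. It does not. The Variables section gives the unit of the rate, and the Statistical analysis section names the periods compared. A mean monthly rate over a year, or monthly values within it, satisfies both. The binary outcome is a declared sensitivity analysis, not a third definition.

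A reader might also infer that the monthly unit alone causes the inflation. The clustered column above shows otherwise: monthly rows with CCG-clustered errors stay near 5%. The cause is treating repeated values as independent, and nothing in the article says outright that this will be done.

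The strongest objection is that a condensed article may leave variance estimation to a fuller plan. That limits the point to a conditional one. It does not remove it, because the article itself fixes the monthly unit, the stacking of two years of the same CCGs as two groups, the command, the adjustment set and the screening rule. It also names a serial-correlation test for the time series and nothing equivalent for the mediation models.

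Three further limits stand. The ICC is unknown. The planned covariates would absorb some between-CCG variance and lower it. Some mediators come from other organisations' data and may not be a single value per CCG.

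**Conclusion.** The point holds as an unresolved specification with a conditional harm. The row unit of the mediation models is not fixed, and nothing accounts for a CCG appearing more than once. With the monthly outcome and independent rows, a null CCG-level mediator could be declared significant about 7-12% of the time at small between-CCG variance and about 35-70% at large. Choosing yearly rows is not a complete remedy: without clustering the rate can reach about 6-18% if strategies pre-date QP. These sizes assume a 5% two-sided test, a mediator constant within the year, and ICCs that the documents do not supply.

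**What to change.** In the Statistical analysis section, state the row for the mediation models. Either:
- use one row per CCG per financial year, with annual or mean monthly items per STAR-PU, which also puts the binary sensitivity analysis on the same rows as the main one; or
- keep monthly rows and add calendar-month terms.

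Under either choice, specify CCG-clustered variance, or a bootstrap that resamples whole CCGs, in every mediator and outcome model. Leave the Abstract's outcome wording and the practice-level time series as they are, since both match the practice-level analyses.

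This takes a few sentences and, for yearly rows, one aggregation of data already planned for use. The price is wider confidence intervals for the indirect effects than independent monthly rows would show.

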**Figure 1 F1:**
[figure not shown]
Conceptual model. The direct effect is represented by the path between the QP initiative (predictor) and antibiotic prescribing rate (outcome). *Not directly observed within our data. AMS, antimicrobial stewardship; CCG, Clinical Commissioning Group; CMO, Chief Medical Officer; QP, Quality Premium; TARGET, Treat Antibiotics Responsibly, Guidance, Education, Tools.

Our conceptual model suggests that in addition to its direct impact, the QP initiative acts by stimulating and enhancing the adoption of existing strategies to reduce and optimise antibiotic prescribing. In investigating the potential pathways connecting QP to reductions in antibiotic prescribing, we will be examining the hypothesis that factors like the Chief Medical Officer’s (CMO) letter, Treat Antibiotics Responsibly, Guidance, Education, Tools (TARGET) toolkit, antibiotic auditing, benchmarking, local incentives at CCG level, prescribers and patients’ antimicrobial stewardship (AMS) education/training can transmit part of the influence of the QP initiative to antibiotic prescribing.

First implemented in September 2014, the CMO letter, which provided social norm feedback to primary care practitioners in England whose antibiotic prescribing rate was in the top 20%, reduced antibiotic prescribing by 3.3% in 6 months in a randomised trial.^26^ The criteria for selecting practices that received the letters in the subsequent years changed with the addition of measures like a change in antibiotic prescribing over time and whether practices have previously been sent CMO letter.

Another important mediator hypothesised in our conceptual model is AMS education/training of prescribers and patients. Educating and training prescribers on the importance of antibiotic stewardship and ways to promote prudence can help prescribers make better decisions on when an antibiotic is indicated and can also improve patients’ knowledge on the appropriate use of antibiotics. AMS interventions targeted at patients can improve their knowledge of when antibiotics are not needed and increase confidence and skills on how to self-care, which can result in reduced consultations for self-limiting illness and thus reduced antibiotic prescriptions.

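### The mediation models omit each CCG's own pre-QP antibiotic prescribing rate, a measured and plausible confounder of the strategy-outcome path that the study will hold

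*Protocol article*

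**What the plan says.** The Variables section introduces the covariates with "To account for differences in practice and CCG characteristics that can contribute to variance in antibiotic prescribing, we will be adjusting for" and then lists the number of GPs, the deprivation index, prevalence of five comorbidities, and "the prescribing rate of other non-antibiotic drugs (opioids and benzodiazepines) and seasonal influenza vaccination rate". The only prescribing covariate is for drugs other than antibiotics. The Statistical analysis section refers back to adjustment for practice and CCG characteristics and adds nothing to the list.

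The missing variable will be available. Under Data sources, "Data for the period 2013 to 2015 will be mapped to CCG level from the practice-level data", and "OpenPrescribing publishes monthly antibiotics prescribing data from August 2013".

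For the mediation models, the Statistical analysis section says that "our dataset for the mediation analyses will have the control group as the financial year before QP", set against one post-QP year at a time. It states no CCG effect, change score or baseline term.

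Two passages bear on who received or adopted the strategies. The conceptual-model text says the Chief Medical Officer's (CMO) letter went to practitioners "whose antibiotic prescribing rate was in the top 20%, reduced antibiotic prescribing by 3.3% in 6 months in a randomised trial". The Variables section says the surveyed antimicrobial stewardship leads reported "adoption of national and local strategies in their respective CCG to enable them to meet QP targets on antibiotic prescribing in primary care".

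**The concern.** The aim is to split the QP effect into direct and indirect parts. The indirect part needs the effect of each strategy on prescribing. If a strategy is largely absent before QP, that effect is estimated by comparing adopting with non-adopting CCGs in the post-QP rows. The 2014/15 control rows do not turn it into a within-CCG comparison.

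A CCG's earlier rate is a natural predictor of its later rate. If it also influences adoption, it confounds the strategy-outcome path. Should high prescribers adopt more, a useful strategy looks weaker than it is; should low prescribers adopt more, it looks stronger. The error would carry forward, because only mediators that show an effect in the single-mediator models enter the sequential model. Even if adoption is unrelated to the prior rate, leaving out a strong predictor costs precision.

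**Working it through.** The protocol gives no SD, correlation, effect size or power figure, so there is no stated calculation to reproduce. What follows is an illustration.

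**From the protocol:** 187 CCGs with mediator data; monthly data from August 2013, hence eight months of 2013/14 (August to March) before the 2014/15 control year.

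**Assumed, not in the protocol:** between-CCG SD 12% of the mean; year-to-year correlation r = 0.7 or 0.93; listed covariates explain R² = 0.4 of stable between-CCG variation; adoption odds ratio (OR) per SD of the 2014/15 rate from 0.8 to 1.5; true strategy effect -2%; strategy coded 0 before QP.

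**Bias, planned model.** To a good approximation, bias = ln(OR) × SD × r(1 - R²).

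**Bias, with the 2013/14 rate added.** Write s = r(1 - R²) and e = 1 - r. The covariance left between the 2014/15 rate and the later rate is s·e/(s + e), so bias = ln(OR) × SD × s·e/(s + e).

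- r = 0.93: s = 0.93 × 0.6 = 0.558, e = 0.07, s·e/(s + e) = 0.062.
- r = 0.7: s = 0.7 × 0.6 = 0.42, e = 0.30, s·e/(s + e) = 0.175.
- ln(1.5) × 12 = 4.87 points; ln(0.8) × 12 = -2.68 points.

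| r | OR | Planned estimate | With 2013/14 rate |
|---|---|---|---|
| 0.93 | 1.5 | -2 + 4.87 × 0.558 = +0.7% | -2 + 4.87 × 0.062 = -1.7% |
| 0.93 | 0.8 | -2 - 2.68 × 0.558 = -3.5% | -2 - 2.68 × 0.062 = -2.2% |
| 0.7 | 1.5 | -2 + 4.87 × 0.42 = +0.0% | -2 + 4.87 × 0.175 = -1.1% |
| 0.7 | 0.8 | -2 - 2.68 × 0.42 = -3.1% | -2 - 2.68 × 0.175 = -2.5% |

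Simulation of the stacked pre/post dataset by least squares gives nearly the same ranges: about -3.4% to +0.6% as planned, and about -2.4% to -1.2% with the 2013/14 rate. A weaker odds ratio of 1.1 at r = 0.93 gives about -1.3% as planned.

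**Precision with no selection (OR = 1), simulated.** At r = 0.7 the standard error falls from about 1.5 to 1.2 points, (1.5 - 1.2)/1.5 = 20%. At r = 0.93 it falls from about 1.4 to 0.64, (1.4 - 0.64)/1.4 = 54%. In terms of sample size, that is (1.5/1.2)² ≈ 1.6 to (1.4/0.64)² ≈ 4.8 times as many CCGs.

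**Alternative model.** Post-year rows only, regressing the rate on the strategy, the covariates and the 2014/15 rate, gives about -2.0%, the true value. It does so because adoption was made to follow the 2014/15 rate.

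**The case against.** **Selection is mostly inferred.** Only the CMO letter is documented as going to high prescribers, and that is selection of practices, not CCGs. For audit, benchmarking, local incentives and education, the protocol says only that adoption served the QP targets. The Introduction words the first target as a cut of 1% of the 2013/14 England mean, 0.01 × 1.61 = 0.016 items per STAR-PU. Read literally, that is the same absolute cut for every CCG, which does not imply more adoption by high starters. This stands. A reader might infer that the strategies are confounded by indication as a fact, or that the answer on mechanisms will be reversed. The text supports neither. Average sign reversal appears only toward the strong end of the assumed selection, and low prescribers adopting more would push the bias the other way.

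**The size depends on an unstated correlation.** This also stands. A reader might take the gain in precision as worth several times as many CCGs, but that holds only near r = 0.93. At 0.7 the gain is modest.

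**Coding the strategy 0 before QP is a simplification.** The conceptual model speaks of enhancing existing strategies, and the CMO letter began in September 2014, inside the control year. This limits the illustration; it does not supply the missing covariate.

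**The protocol is not silent.** Sensitivity analyses includes whether each CCG met its required reduction, an outcome based on change. Limitations says the causal reading rests on sequential ignorability and concedes unmeasured confounders. Neither resolves the point. The prior rate is measured, and the change-based analysis is a dichotomised sensitivity check. A plain change score can also over-correct when adoption follows the 2014/15 rate: in a separate simulation (SD 15%, true effect -3.3%, correlation 0.9, covariates explaining half of stable variation) it averaged -3.8% to -4.3% with selection. The prior rate is otherwise used only to form practice-level subgroups.

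**Conclusion.** The point holds as an avoidable omission and should be fixed. The stated adjustment set leaves out a measured variable that probably predicts the outcome strongly and may drive adoption. What is exposed is the strategy-outcome path, and through it the direct/indirect split. The total pre/post contrast compares largely the same CCGs, and the interrupted time series uses a national mean, so neither is affected.

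The protocol does not fix the direction or size of any bias. In the illustration, the worst average departure from a true -2% is about 2.6 points as planned (from -2% to +0.6%) and about 0.8 points with the 2013/14 rate (from -2% to -1.2%). With no selection there is no bias, and the benefit is a standard error smaller by about 20% to 54%. All of these figures rest on the assumed SD, covariate R², correlation and odds ratios.

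**What to change.** In the Variables section, add the CCG's antibiotic items per STAR-PU for August 2013 to March 2014 as a covariate. Include it in both the mediator and the outcome model of every single- and multiple-mediator analysis. The 2014/15 rate cannot serve in the stacked dataset, because it is the outcome in the control rows.

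The earlier rate removes the bias only in part. Add, as a sensitivity analysis, a strategy-outcome model in the post-QP year alone, conditional on the 2014/15 rate.

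The cost is one covariate and one extra model, both from data already planned. The baseline covers eight of twelve months, which should be stated. Merged CCGs need averaged baseline values, in line with the rule already given under Handling missing data.
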